### Ethical considerations

2.9

Institutional Review Board (IRB) at Sangath, India has approved all study procedures. Written informed consent will be mandatory for enrolling ASHAs in this trial. Participation in the study is completely voluntary and ASHAs can decline participation or withdraw at any time without any consequence to their current employment as health workers. Health system officials will have no role in the consent process to minimize possible influence. Trial research assistants will be given periodic refresher training to observe their skills in administering consent and providing supportive feedback. Confidentiality of participants will be protected using unique study ID numbers, and by separating study data from participant-identifiable data. The research team will submit study progress reports, including serious adverse event (SAE) reporting, flow charts, and baseline characteristics of enrolled ASHAs and patients across the study arms to the IRB on a periodic basis. The team will maintain a file of all required regulatory documents, study-specific documents, IRB approval notices, IRB-approved consent documents, and all correspondence with the IRBs that will be available any time for study audit.

With respect to the temporary absence of intervention arm ASHAs from their village-level activities due to the 5-day residential workshop, we have duly considered the same. We want to highlight that we will provide 7–10 days for the ASHAs when telephonically inviting them in advance of their participation in the workshop, which will give them sufficient time to plan the activities in their village due to their absence. In addition, we will coordinate with the ASHA supervisor for the same, so her support is elicited in performing some of the health care duties in the village as needed. Further, a permission letter from the district-level Chief Medical and Health Officer (CMHO) will be obtained prior to inviting ASHAs for the residential workshop.

### Trial management

2.10

The Senior Management Team (SMT), consisting of the principal investigator, co-investigators, and study collaborators, in addition to research and intervention coordinators, outcome evaluators, and data manager, will provide overall trial leadership and will meet at least every 7–14 days to review trial progress, participant recruitment, data collection, process indicators, and any safety concerns or other issues that may arise. The team will submit annual reports to the Sangath IRB, in addition to progress reports to the state health department.

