### Blinding

2.5

Research coordinators and research assistants administering study assessments to ASHAs and patients, will be blind to participant allocation, and study investigators (except data manager) will also be blind to participants’ experimental condition. Participants will be told their arm allocation only after consent and baseline assessment. There is complete separation between the team members involved in developing or delivering the intervention and assessing intervention fidelity and process indicator data (2.3.5.2 and 2.4.4), and the team members involved in administering the outcome assessments (2.4.1 to 2.4.3). Outcome team members and investigators will be unblinded after the completion of analysis of data of baseline, 1-, 3- and 6-month follow-up assessments.

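### The management team in section 2.10 has blinded outcome staff and investigators reviewing intervention-arm process indicators, which conflicts with the complete separation promised in section 2.5

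*Protocol article*

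**What the plan says.** Section 2.5 (Blinding) makes three commitments.

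- On assessors: "Research coordinators and research assistants administering study assessments to ASHAs and patients, will be blind to participant allocation".
- On investigators: "study investigators (except data manager) will also be blind to" the experimental condition. The data manager is the only stated exception.
- On team structure: "There is complete separation between the team members involved in developing or delivering the intervention and assessing intervention fidelity and process indicator data" on one side, "and the team members involved in administering the outcome assessments" on the other.

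It adds that the outcome team and the investigators are unblinded only once the baseline, 1-, 3- and 6-month data have been analysed.

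Section 2.10 (Trial management) describes a Senior Management Team made up of the principal investigator, co-investigators and collaborators, "in addition to research and intervention coordinators, outcome evaluators, and data manager". This team "will meet at least every 7–14 days to review trial progress, participant recruitment, data collection, process indicators, and any safety concerns".

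**The concern.** Section 2.5 names process indicator data as something that outcome staff are kept apart from. Section 2.10 then has outcome evaluators, research coordinators and investigators review that same category of data, beside the intervention coordinators and the data manager, whom 2.5 exempts from blinding.

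Participants learn their arm after baseline, so the masking in this single-blind trial rests on the assessors and the investigators. If either group learns which ASHA is in which arm, three things weaken:

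- the neutrality of the research assistant who conducts the patient's endline PHQ-9 and satisfaction assessment (section 2.3.3), from which remission rates are compared between arms (section 2.8);
- the standardised handling of ASHAs' queries, which the Discussion relies on to limit socially desirable answers;
- the claim that investigators stay blind through analysis.

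**Working it through.** No arithmetic applies. The check is whether sections 2.4.4, 2.5 and 2.10 can all hold as written.

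1. **Who is in the meeting.** Section 2.10 names investigators, research coordinators, intervention coordinators, outcome evaluators and the data manager. Section 2.5 declares the research coordinators who administer assessments and the investigators blind, and puts those who administer outcomes on the separated side. It exempts the data manager. Intervention coordinators, by their role, belong to the delivery side. The meeting therefore joins the two sides.

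2. **What the meeting reviews.** The listed agenda is to "review trial progress, participant recruitment, data collection, process indicators, and any safety concerns". Process indicators are named explicitly, so this is not inferred from a general reference to progress.

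3. **What the indicators are.** Section 2.4.4 lists workshop attendance, withdrawals during and after the workshop, the knowledge test before and after it, days from workshop to first call, number and average duration of calls, rescheduling patterns, and dropouts in the coaching phase. The control arm has no workshop and no coaching calls, so every one of these items arises only in the intervention arm.

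4. **Whether they can reveal individuals.** Some items are counts or averages (attendance per batch, mean days to first call, mean call duration). These do not show which ASHA is in which arm. Withdrawals, rescheduling and dropouts are events of individual ASHAs. If such a case is discussed by name or study ID, that ASHA is identified as an intervention participant. Section 2.10 does not say at which level the indicators are shown.

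5. **Whether a safeguard is stated.** No section provides for closed sessions, recusal of blinded members or aggregate-only reporting to them.

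Steps 1 to 3 establish the conflict between 2.5 and 2.10. Steps 4 and 5 establish an unprotected route to individual allocation, but not that the route is used.

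**The case against.** The best counter-argument is that section 2.5 separates tasks. The people who deliver the intervention and collect its process data are not the people who administer outcomes, and sitting on a common leadership team does not change that. Meeting rules are also commonly left to a charter or full protocol. This has some force: section 2.4.4 does assign collection of the indicators to the intervention development team. It does not remove the conflict. Section 2.5 calls the separation complete and names process indicator data within it, while 2.10 expressly makes outcome staff reviewers of those data. The difficulty is what the article states, not a detail it leaves out.

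Other limits stand:

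- A reader might infer that assessors will be told individual allocations. The text does not say so; several indicators are aggregates, and knowing that an intervention arm exists reveals nobody's allocation.
- Section 2.10 does not name research assistants as team members. Any effect on the patient PHQ-9 needs knowledge to pass to them from coordinators or evaluators, or the roles to overlap.
- The AHI is self-administered on paper by ASHAs who know their arm, and the Discussion promises standard procedures for answering queries. Assessor knowledge has little room to act there.
- A reader might treat assessor blinding as the only masking. Section 2.5 also blinds investigators.
- A reader might multiply the meeting interval over the trial's calendar to size the problem. That would count meetings after intervention activities are due to end (September 2024), and a number of meetings does not measure bias.
- The intervention lead runs the workshops and reviews coaching calls, so cannot be blind to who attends. This contradicts 2.5 only if that person is a study investigator, which the available text does not show.

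**Conclusion.** The point holds as a contradiction between sections 2.5 and 2.10. The plan as written does not secure the complete separation and the investigator blinding that it claims. The consequence is a risk that blinded staff learn individual allocations, with no stated safeguard; the documents do not support saying that blinding is or will be broken.

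The size of any bias cannot be computed from the documents. For the primary outcome it is likely limited, because the AHI is self-reported by participants who know their arm. The patient PHQ-9 remission comparison is more exposed, on two assumptions: that the research assistant conducts the endline as section 2.3.3 says (section 2.4 describes all questionnaires as self-administered), and that knowledge reaches that assistant. The claimed blinding of investigators is affected more directly, since they are members of the reviewing team. The change is worth making because it restores a stated safeguard at very little cost.

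**What to change.** Reconcile sections 2.5 and 2.10 by splitting the Senior Management Team meeting.

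- **Open session, all members:** recruitment, data collection and pooled safety counts.
- **Closed session, without outcome evaluators, research coordinators or any other blinded member:** process indicators and any participant-level intervention matter.
- **Section 2.5:** list which roles are unblinded. An investigator who has to see process indicators should appear on that list and not be described as blind.

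The cost is one protocol paragraph and a change to the meeting agenda. Sample size, outcomes, treatment and analysis are unaffected.

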## Discussion

3

Our intended impact is to demonstrate improved wellbeing of frontline health workers by the delivery of a character-strengths based coaching intervention. The expected study results will position our team to propose this intervention model to be adopted by wider stakeholders. Importantly, these stakeholders include key cadres of frontline workers in India including ASHAs in other districts and states, Auxiliary Nurse Midwives who are health facility based, Aanganwadi Workers who work towards improving child nutrition and growth, as well as community health officers (CHOs) in sub-health centres. There are more than a million ASHAs in India (one of the largest community health worker programs in the world [7]) and this study would pave the way for addressing one of their most pressing challenges i.e., poor mental wellbeing and burnout. Given the evidence-base, improved wellbeing can contribute to improved service delivery with a consequent benefit to patients and communities [[65], [66], [67], [68], [69]]. Therefore, the trial is positioned to strengthen the overall primary care system by first improving the wellbeing and reducing burnout among ASHAs with the consequent improvement in delivery of their frontline services.

From the perspective of challenges at a broader level, we want to mention that post-pandemic, the government has also introduced training modules for ASHAs to make them aware of mental health conditions and coping with mental stress. While the ‘seeding’ of ASHAs by knowledge of mental health will affect all trial ASHAs, across both arms, we will consider gathering qualitative data on these aspects through the course of the trial, particularly during the focus group discussions (section 2.4.6). Another challenge could be the aspect of socially desirable response patterns in the answers provided to psychometric tools, especially given that ASHAs work at the bottom of system hierarchies. This will be addressed by standardised procedures of providing instructions to ASHAs during outcome assessment (e.g., emphasis on ‘no right and wrong answers’, standard operating procedures for outcome assessors to clarify ASHAs' queries, and providing a comfortable environment for outcome assessment).

We will disseminate our trial findings through conference presentations at leading international scientific meetings, as well as national meetings in India. From a scalability perspective, towards the end of the project, we will organize a 2-day Dissemination Workshop with relevant health system stakeholders and policymakers to share our findings and increase the uptake of evidence, particularly in the state government programs focusing on capacity-building, mental health and/or wellbeing of ASHAs.

### Trial status

3.1

Enrolment for this trial started in January 2024 and is expected to complete by June 2024. Intervention activities are expected to complete by September 2024 and terminal follow-up outcome assessments by December 2024.

## Conclusion

4

This trial will provide early evidence on the effectiveness of a character-strengths based coaching intervention to reduce work stress among rural frontline health workers in India, to inform similar interventions globally, particularly for the rural women cadres. Our study critically contributes to the broader positive psychology literature on the use of character-strengths for building capacities among frontline workers in low-resource settings to address/respond to work-stress.

## Ethics approval

Institutional (ethics) Review Board at Sangath, India approved all study procedures.

## Consent

All participants provided written informed consent for the study activities.

## Data Availability

Data will be made available on request.
